### Statistical analysis

The final data will be entered and counted by a professional statistician using SPSS 26.0 (IBM, Armonk, NY, USA). For continuous variables, the normality of measured data distributions will be evaluated using the Shapiro-Wilk test. Measurements will be expressed as mean ± standard deviation, if the data are normally distributed with uniform variance. Paired *t*-tests will be used for within-group comparisons before and after treatment, and independent samples *t*-tests will be used for between-group comparisons before and after treatment. If the data do not conform to a normal distribution or have an uneven variance, the measurement data will be expressed as median (interquartile range) [M(Q)] and the Wilcoxon rank sum test will be used for the analysis of the data before and after treatment. For categorical variables, chi-square tests or Fisher’s exact tests will be used to examine differences between groups and to describe effect sizes in terms of percentages and frequencies. Prior to any analysis, the pattern and reasons for missing data patterns will be investigated. The primary analysis will be conducted as an intention-to-treat analysis, which includes all participants with missing outcome data, unless there is clear evidence that its underlying assumption is inappropriate. Multivariable imputation by chained equations method will be used to impute missing data for the sensitivity analysis for the primary and secondary outcomes. *P*<0.05 indicates that the threshold of statistical significance has been reached.

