### Randomization and blinding

Prior to the start of the study, randomization will be performed using a computer-generated table of random numbers by the research pharmacy not involved in the screening of subjects. Included participants will be randomly assigned with a 1:1 allocation to either the lidocaine or placebo group, with each patient having an equal probability of being assigned to either the experimental treatment group or the placebo group. The material, size and colour of the placebo patch will be similar to LP5 as far as possible. Patients will use the patches under the guidance of their surgeons. The group allocation protocols will be enclosed in opaque envelopes to ensure blinding of the investigators, patients, and data analysts. These envelopes will be sealed and could only be opened after the study is completed.

If a subject experiences a serious adverse event or requires emergency resuscitation during the trial, whether or not it is related to the intervention, the intervention received by the subject will be disclosed. Subjects who disclose the intervention will be considered as drop-out cases. If the intervention is disclosed for more than 20% of participants, the trial will not be considered double-blind.

In addition, the allocation scheme of the intervention will be confidential to the evaluators collecting outcome data throughout the study. The statistical analysts will also not know whether participants are in the LP5 or placebo group until the statistical analysis is completed.

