#### Primary outcome

The primary outcomes will be the changes from the baseline of the American Shoulder and Elbow Surgeons score (ASES) [22] at the completion of the 90-day follow-up.

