### Statistical methods

#### Sample size calculation

There are no reports in the available literature relating to the primary outcome. A pre-trial with a sample size of 60 was conducted in our orthopaedic clinic. 3-month follow-up time results showed ASES scores of 63.56 ± 15.56 and 74.94 ± 18.42 in the control and intervention groups, respectively. With a type I error rate of 0.05 (*α* = 0.05, two-tail) and a power of 90% (*β* = 0.10), the sample size for the study protocol was calculated as 41 patients per group based on the primary outcome indicator by PASS 15.0 (Power Analysis and Sample Size, NCSS, LLC, USA). Assuming a 20% drop-out rate, we plan to recruit 102 participants (51 per group) to the study.

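### The primary outcome is change in ASES, but the planned between-arm test does not say whether it compares change or the day-90 score; a baseline-adjusted model would settle this and gain precision

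*Protocol article*

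**What the plan says.** Three sections of the protocol article bear on the primary comparison.

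- **Primary outcome.** "The primary outcomes will be the changes from the baseline of the American Shoulder and Elbow Surgeons score (ASES", assessed at the end of the 90-day follow-up. The abstract agrees.
- **Sample size calculation.** The inputs are scores at follow-up, not changes: "3-month follow-up time results showed ASES scores of 63.56 ± 15.56 and 74.94 ± 18.42 in the control and intervention groups, respectively". From these, "the sample size for the study protocol was calculated as 41 patients per group based on the primary outcome indicator". No SD of change and no correlation between baseline and follow-up is given.
- **Statistical analysis.** Paired t-tests are assigned to comparisons within each arm. For the arms against each other, independent-samples t-"tests will be used for between-group comparisons before and after treatment". If the data are non-normal or the variances unequal, a Wilcoxon rank sum test takes over. No baseline covariate is named.

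Table 1 schedules ASES at baseline, day 30 and day 90, so the baseline value will be available.

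**The concern.** The wording for the between-arm test fits at least two analyses: a t-test on the day-90 score and a t-test on the change from baseline. They have different standard errors and can give different p-values on the same data. A primary analysis should leave no such choice open once data are in.

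The test that clearly uses change is the paired t-test within each arm. It does not estimate the effect of the patch: both arms have the repair and the same rehabilitation, so both may improve, and a significant change in one arm is not a contrast with the other.

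The sample size is described as based on the primary outcome but uses the spread of raw scores. If change is what is analysed, its SD is the relevant one, and the reader cannot tell whether it is larger or smaller. An unadjusted test of either kind also gives up precision that the baseline ASES could supply.

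**Working it through.** **Inputs from the sample size section.** Control 63.56 (SD 15.56), intervention 74.94 (SD 18.42), two-sided alpha 0.05, power 90%, 41 per group, 20% drop-out, 51 per group recruited. 51 × 0.8 = 40.8, so 41 evaluable per arm is the right number to test.

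**The plan's own figure.** The difference is 74.94 − 63.56 = 11.38. The pooled SD is √((15.56² + 18.42²)/2) = 17.05. The normal approximation gives n = 2 × (17.05 × (1.960 + 1.282)/11.38)² = 47.2, so 48 per group; the t-test (equal-variance or Welch) needs 49. The stated 41 is not reproduced. A two-sided t-test gives exactly 41 if the control SD of 15.56 is used for both arms (power 90.5%). With 17.05 and 41 per arm, the t-test on the raw day-90 score has 84.7% power. This drop from 90% to 85% is a sample-size matter, separate from the choice of analysis.

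**Change score and ANCOVA.** Under randomisation the expected difference between arms is the same for the change as for the day-90 score, because the expected baseline difference is zero. Only the SD differs. Let rho be the correlation between baseline and day-90 ASES. Neither rho nor the baseline SD is in the document. I assume the baseline SD is also 17.05 and vary rho.

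- SD of change = 17.05 × √(2(1 − rho))
- Residual SD under ANCOVA = 17.05 × √(1 − rho²)

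Power is from the noncentral t with 41 per arm and difference 11.38, ignoring the one degree of freedom spent on the covariate; n is per group for 90% power.

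| rho | SD of change | Power, change | n, change | ANCOVA SD | Power, ANCOVA | n, ANCOVA |
|---|---|---|---|---|---|---|
| 0.2 | 21.57 | 66% | 77 | 16.71 | 86% | 47 |
| 0.3 | 20.17 | 71% | 68 | 16.26 | 88% | 44 |
| 0.4 | 18.68 | 78% | 58 | 15.63 | 90% | 41 |
| 0.5 | 17.05 | 85% | 49 | 14.77 | 93% | 37 |
| 0.6 | 15.25 | 92% | 39 | 13.64 | 96% | 32 |
| 0.7 | 13.21 | 97% | 30 | 12.18 | 99% | 26 |

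The raw day-90 score has 85% power and needs 49 per group at every rho.

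**Relative precision.** Against the change score, the ANCOVA variance is (1 − rho²)/(2(1 − rho)) = (1 + rho)/2: 60% at rho 0.2, 75% at 0.5, 85% at 0.7. Against the raw score it is 1 − rho²: 96%, 75% and 51%. For rho between 0 and 1 ANCOVA beats both. Its treatment effect is the same whether the dependent variable is the day-90 score or the change, so it removes the ambiguity.

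**The case against.** The phrase about between-group comparisons before and after treatment can be read as comparing the before-to-after change between arms, with the primary outcome section supplying the variable. That stands. A reader might infer that the protocol never compares change between arms; the text does not show that, only that it fails to say.

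A reader might also infer bias. An unadjusted t-test on either variable is valid under randomisation, and chance imbalance at baseline is already covered by the type I error rate. What adjustment buys is precision.

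Nor does the protocol present the paired tests as evidence of efficacy. It declares a placebo-controlled superiority trial and lists a between-arm test beside them.

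The hardest objection concerns power. It rests on two values the document lacks, and the direction is open: with equal SDs the change score loses to the raw score below rho 0.5 and gains above it. Nor is 17.05 shown to be the SD used in planning. If 15.56 was used, the SD of change exceeds it whenever rho is below 1 − (15.56/17.05)²/2 = 0.58. So a definite loss of power cannot be claimed.

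An analysis plan that is not shown might add covariates. But the protocol itself fixes the tests, and its wording is what needs settling.

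**Conclusion.** The point holds as an ambiguity in the primary contrast and a loss of precision that can be avoided. The outcome definition, the sample-size inputs and the named test do not identify one analysis, and the within-arm tests cannot stand in for it.

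The size is conditional. Assuming equal SDs of 17.05, a difference of 11.38 and 41 evaluable per arm, power for a t-test on change runs from 66% at rho 0.2 to 97% at rho 0.7, and for ANCOVA from 86% to 99%. The gain is large when rho is low and small when it is high. ANCOVA reaches 90% with 41 per arm only if rho is about 0.4 or more.

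It would be tempting to conclude that the trial is underpowered for its declared outcome because raw scores were used for sizing. The document does not support that: above rho 0.5 the change score does better than the raw score. The shortfall from 90% to 85% for the raw score comes from the figure of 41, which the two stated SDs do not reproduce, and should be dealt with as a separate matter.

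Confidence is high on the ambiguity and on the precision gain; the actual power stays unknown until rho is given. This should be corrected, but it does not invalidate the design.

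**What to change.** Replace the wording for the primary comparison with: *The primary analysis is the LP5-placebo difference in ASES at day 90 from a linear model with treatment and baseline ASES, reported with a 95% confidence interval and two-sided p-value. This analysis will not be replaced on the result of a normality or variance test; a rank-sum test will be a sensitivity analysis.* Without the second sentence, the existing fallback could still displace the adjusted model.

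For the other continuous outcomes, adjust for their own baseline where a linear model suits the scale. This should not be automatic for internal rotation, which is coded as a vertebral level capped at 18. Outcomes measured at several visits, such as VAS and PPT, also need the visit named. Keep the within-arm paired tests as description only.

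In the sample size section, restate power for the adjusted analysis using rho from the 60-patient pre-trial, and say which SD produced 41.

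The cost is wording and one recalculation. Baseline ASES is already scheduled and the named software fits the model. The recalculation needs baseline ASES from the pre-trial, which the protocol does not say was recorded; failing that, a range of rho should be shown. The change should be made before allocation is revealed and go through the protocol's amendment route to the ethics committee and the registry.

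### A normality and variance pre-test chooses the test and estimand for the primary ASES comparison, and the only fallback named, the rank-sum test, does not fit paired data or unequal variances

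*Protocol article*

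**What the plan says.** All of this stands in the Protocol article.

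- **Primary outcome:** change in ASES from baseline to the end of the 90-day follow-up. No analysis rule is given for it alone.
- **Statistical analysis, preliminary check:** for continuous variables, "the normality of measured data distributions will be evaluated using the Shapiro-Wilk test". Variance must also be uniform, but no variance test is named.
- **Statistical analysis, if the checks pass:** paired t-tests "will be used for within-group comparisons before and after treatment", and independent-samples t-tests "will be used for between-group comparisons before and after treatment".
- **Statistical analysis, if they fail:** "If the data do not conform to a normal distribution or have an uneven variance", results become medians with interquartile ranges and "the Wilcoxon rank sum test will be used for the analysis of the data before and after treatment". Neither the signed-rank test nor Welch's t-test is mentioned anywhere.
- **Sample size calculation:** the trial is sized on pre-trial "ASES scores of 63.56 ± 15.56 and 74.94 ± 18.42 in the control and intervention groups", two-sided alpha 0.05 and 90% power, giving 41 per group before drop-out. This is a comparison of means.

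**The concern.** The rule has three weaknesses.

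1. **The primary test is not fixed.** The data decide whether the trial reports a difference in mean ASES change or a rank comparison summarised by medians. These answer different questions, and only the first matches the sample size calculation. One data set could be called significant under one branch and not under the other. Because the variance check is unnamed, two analysts could take different branches.
2. **Unequal variance alone triggers the rank-sum test.** For a comparison of means, that test does not correct for unequal spread. Welch's t-test does.
3. **The paired/independent distinction disappears in the fallback.** The t-test branch keeps the two designs apart. The fallback names a single test, which assumes independent samples, and a patient's baseline and follow-up scores are not independent.

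At stake are a primary result that may come without a difference in ASES points, a choice of test open to challenge, and wrong p-values for the within-group results.

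**Working it through.** **Inputs from the Sample size calculation section.** Means 63.56 and 74.94, so the difference is 11.38. SDs 15.56 and 18.42, so the SD ratio is 18.42/15.56 = 1.18. Two-sided alpha 0.05; 41 per group.

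**Assumptions, because the document gives no value.** Levene's test at 0.05 for variance; Shapiro-Wilk at 0.05 in each arm; the SDs of the 3-month scores used for the analysed variable; within-patient correlation r as stated below.

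**Step 0: the plan's own figure.** Root-mean-square SD = √[(15.56² + 18.42²)/2] = √[(242.11 + 339.30)/2] = 17.05. Then n = 2 × (1.960 + 1.2816)² × 290.70/129.50 = 47.2, so 48 per group (49 with the t distribution). The stated 41 is not reproduced with both SDs; a t-based calculation with the control SD alone gives 41. That is a separate issue. Here 41 serves only as the analysed arm size, which is why power below is about 85% (t-based 0.847) and not 90%.

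**Step 1: how often the rule switches, normal data.** Expected Shapiro-Wilk rejection in at least one arm: 1 − 0.95² = 9.8%; simulated 10.0%. Levene at the pre-trial SDs: simulated 16.4%. Treated as independent, 1 − 0.900 × 0.836 = 24.8%; simulated 24.9% over 20,000 trials, with other runs at 23% to 25%. At 51 per group it is 27%. With equal SDs it is still 13%.

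**Step 2: what the switch does to the primary comparison (normal data, pre-trial SDs).**

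| Quantity | Pre-test rule | Welch |
|---|---|---|
| Type I error, 51 per group | 0.054 | 0.051 |
| Power, 41 per group, difference 11.38 | 0.838 | 0.845 |

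Another run of the rule at 41 per group gave type I error 0.048. With 5,000 trials the simulation standard error at 5% is √(0.05 × 0.95/5000) = 0.003, so these values are close to nominal. At the planning values, rank-sum and Welch gave different significance verdicts in about 5% of trials (4% to 6% across runs).

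**Step 3: rank-sum under unequal variance, equal means, nominal 0.05.** SD ratios above 1.18 and unequal arms of 51/36 (larger SD in the smaller arm) are assumptions.

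| SD ratio | Rank-sum, 51/51 | Rank-sum, 51/36 | Welch, both layouts |
|---|---|---|---|
| 1.18 | 0.052 | 0.053 | 0.049–0.052 |
| 2 | 0.058 | 0.073 | 0.049–0.051 |
| 3 | 0.067 | 0.086 | 0.049–0.051 |

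If the variable were also gamma-skewed (assumed), rank-sum at ratio 1.18 and 51/51 would reject in 0.065 against 0.050 for Welch. The effect at the document's own ratio is small.

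**Step 4: rank-sum on paired data (41 pairs, assumed r = 0.5, SD 17, shift 6).** The true standard error of the mean change is 17 × √[2(1 − 0.5)/41] = 2.655. A test that ignores pairing uses a standard error larger by 1/√(1 − 0.5), so its effective critical value is 1.960/0.7071 = 2.772. In normal approximation the two-sided type I error is about 0.6%. Power is Φ(6/2.655 − 2.772) = Φ(−0.51), about 30%, against Φ(2.26 − 1.96) = Φ(0.30), about 62%, with pairing. Simulation of the actual rank tests gives:

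| Test | Type I error | Power |
|---|---|---|
| Rank-sum | 0.9% | 28% |
| Signed-rank | 5.0% | 58% |

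With 51 pairs, rank-sum type I error is 0.050, 0.021, 0.007 and 0.001 at r = 0, 0.3, 0.5 and 0.7. Signed-rank stays at 0.046 to 0.050.

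**The case against.** The strongest reply is that little changes numerically. At the only SDs in the document, the rule holds its error rate and costs under one percentage point of power. That stands, and it sets the severity.

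Second, if the patch does nothing at all, randomisation gives both arms the same distribution and the rank-sum test is valid. It is a legitimate between-group test under non-normality. That also stands. The complaint about unequal variance is therefore about what is being compared (means), not about validity under a strict null of no effect.

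Third, the article uses the same before-and-after phrase for its between-group t-test, so the fallback sentence may mean between-group comparisons only. That is a fair reading, but it leaves the within-group comparisons with no fallback. On either reading, within-group tests are not the randomised contrast, and the error on paired data is conservative: it hides changes and does not create them.

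Fourth, an analysis plan may exist. That would excuse missing detail. Here the article states a rule, and the stated rule is the problem.

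A reader might go further and infer that the rule will almost always switch, or that it seriously inflates type I error, because ASES is a bounded score that can be skewed near its upper end. The documents do not support this. Such results need either the raw 90-day score as the analysed variable or SDs that the article does not give, whereas the stated primary outcome is the change score. In an assumed change-score scenario (baseline mean 45, SD 17, r = 0.3), the rule switched in 19% to 21% of trials. Rank-sum type I error was 4.7% against 4.9% for Welch, and power was equal (69.7% and 69.8%).

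**Conclusion.** The concern holds as a should-fix point. The article lets preliminary tests, one of them unnamed, choose both the test and the estimand for the primary outcome of a trial sized on a mean difference. With normal data, the pre-trial SDs, 41 per group and Levene's test assumed, the branch changes in about a quarter of trials and the significance verdict depends on the test in about 5%. Type I error stays close to 5% and power near 84% to 85%, so a claim of gross error inflation is not warranted. The rank-sum test is also the wrong response to unequal variance when means are compared. For paired within-group data it is either invalid or, on the narrower reading, leaves a gap; this touches secondary within-group results only. The paired-data figures rest on the assumed r of 0.5, SD of 17 and 6-point shift. The switching rate rests on Levene's test and on applying the SDs of the 3-month scores to the analysed variable.

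**What to change.** Replace the fallback wording in Statistical analysis with two sentences.

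1. The primary analysis is the between-group difference in mean ASES change from baseline to 90 days, with a confidence interval, whatever any normality or variance check shows. Use Welch's t-test, or a baseline-adjusted linear model with heteroscedasticity-robust standard errors, with one of the two chosen now. The Wilcoxon rank-sum test is reported as a sensitivity analysis.
2. Within-group before-after comparisons use the paired t-test, with the Wilcoxon signed-rank test as the rank-based counterpart.

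The cost is wording only: no extra patients, visits or data. The Trial status section describes the trial as still recruiting, so the change can be made through the article's own amendment route before allocation is unmasked.

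### The primary analysis is labelled intention-to-treat, but as written it omits anyone without a 90-day ASES, because imputation is kept for the sensitivity analysis

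*Protocol article*

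**What the plan says.** All of this is in the protocol article.

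- **Primary outcome:** change in ASES from baseline to the end of the 90-day follow-up, so each participant needs a 90-day score.
- **Statistical analysis, tests:** for continuous data, "independent samples *t*-tests will be used for between-group comparisons before and after treatment". If normality or equal variance fails, "the Wilcoxon rank sum test will be used for the analysis of the data before and after treatment".
- **Statistical analysis, population:** the primary analysis is intention-to-treat, "which includes all participants with missing outcome data, unless there is clear evidence that its underlying assumption is inappropriate".
- **Statistical analysis, missing data:** "Prior to any analysis, the pattern and reasons for missing data patterns will be investigated". After the intention-to-treat sentence comes "Multivariable imputation by chained equations method will be used to impute missing data for the sensitivity analysis for the primary and secondary outcomes".
- **Sample size calculation:** 41 per group are needed. "Assuming a 20% drop-out rate, we plan to recruit 102 participants (51 per group) to the study".
- **Withdrawal and termination criteria:** participants may leave at any time for any reason, through loss to follow-up, or after a serious adverse event or allergic reaction.
- **Randomization and blinding:** treatment is disclosed after a serious adverse event or emergency resuscitation, related or not. "Subjects who disclose the intervention will be considered as drop-out cases". Analysts stay blind to group until the analysis is finished.
- **Table 1:** ASES at baseline, day 30 and day 90; VAS at baseline and days 1, 7, 14, 30 and 90.

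**The concern.** The population sentence promises that participants with missing outcomes are in the primary analysis, but no stated method puts them there. A t-test or rank sum test on the 90-day change uses only participants who have that change. The one method that could bring in the others is placed in the sensitivity analysis. A reader of the trial report would see an intention-to-treat label on a completers' comparison.

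This matters because the listed routes out of the trial can be related to treatment or recovery: serious adverse events, allergic reactions, withdrawal for any reason, and unblinding counted as drop-out. If loss works differently in the two arms, the headline difference is shifted. The primary tests also make no use of the day-30 ASES and the VAS scores that many non-completers will have given.

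The exception attached to the population sentence adds a second weakness. It allows a departure from the primary analysis without saying which assumption is meant, what would count as clear evidence against it, or what would be done instead.

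**Working it through.** **1. The plan's own numbers.** Inflating 41 per group for 20% loss gives 41 / (1 − 0.20) = 51.25. The plan states 51, one short of rounding up, which does not matter here. In reverse, 51 × 0.80 = 40.8, or about 41 completers per arm and 82 in total. Expected non-completers are 102 × 0.20 = 20.4, about 20. The trial is thus sized on the completers that the t-test would use, which fits a complete-case primary analysis. (Whether 41 follows from the pre-trial means and SDs is a separate question.)

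**2. Label against method.**

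| Element of the plan | Can it use a participant without a 90-day ASES? |
|---|---|
| Intention-to-treat sentence | Says yes |
| Independent t-test on change | No |
| Wilcoxon rank sum test | No |
| Chained-equations imputation | Yes, but sensitivity analysis only |

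Nothing in the primary analysis delivers what the first row promises.

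**3. When this biases the difference.** In each arm let *p* be the fraction missing and *g* the completers' mean change minus the non-completers' mean change. The mean over all randomised in that arm is the completers' mean minus *p* × *g*. For arms A and B, therefore:

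bias of the completers' difference (A minus B) = *p*A × *g*A − *p*B × *g*B

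This is zero when the two products are equal, for example when both arms share the same loss and the same gap.

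**4. Size.** The 20% is the plan's drop-out allowance. The gap is my assumption; the documents give none. Take 20% missing in both arms, with loss in arm B random (*g*B = 0):

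| Assumed gap in arm A | Bias | Share of 11.38 |
|---|---|---|
| 5 points | 0.20 × 5 = 1.0 | 1.0 / 11.38 = 9% |
| 10 points | 0.20 × 10 = 2.0 | 2.0 / 11.38 = 18% |
| 15 points | 0.20 × 15 = 3.0 | 3.0 / 11.38 = 26% |

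The 11.38 is the pre-trial difference in 90-day ASES, 74.94 − 63.56. If the non-completers with poorer results are in the lidocaine arm, the benefit is overstated; if they are in the placebo arm, it is understated. The documents do not indicate which.

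**5. What could be recovered.** By Table 1, a participant lost between day 30 and day 90 has a baseline and a day-30 ASES and VAS scores up to day 30. A participant lost before day 30 has no postoperative ASES, only baseline data and whatever early VAS was recorded.

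**6. The exception clause.** Three things would be needed to apply it: the assumption, the criterion and the replacement. None is given. Its trigger would presumably be the review of missing-data patterns and reasons that the same section places before any analysis.

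**The case against.** A complete-case primary analysis with imputation as a sensitivity analysis is a recognised, if weaker, choice. Readers would see whether the result survives imputation. The article condenses a fuller protocol, and details such as imputation covariates or delta adjustment commonly belong in an analysis plan that is not shown. That stands for the details. It does not remove the conflict, because the article itself assigns imputation to the sensitivity analysis and also claims that participants with missing outcomes are included.

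A reader might also infer four stronger things, which the documents do not support:

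- **That the exception clause lets the sponsor abandon intention-to-treat and choose another population after seeing results.** No other population is named. The assumption referred to may be one about missing data. The review precedes analysis, and analysts are blind to group. What would be seen is the missingness pattern, not treatment effects. The supportable criticism is that the clause is undefined.
- **That a complete-case t-test must be biased whenever loss is related to recovery.** Equal loss and equal gaps cancel in the between-arm difference.
- **That 20 outcomes will be missing.** The 20% is a recruitment allowance, and the article plans close follow-up, telemedicine and reminders.
- **That the plan wastes postoperative ASES data on every drop-out.** Those lost before day 30 have none, and the planned sensitivity imputation could use the rest.

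**Conclusion.** The point holds in this form: the intention-to-treat claim cannot be carried out with the primary tests named, so as written the primary result is a complete-case analysis of about 82 of 102 participants if the 20% allowance is used up. That conclusion rests on the text alone.

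Whether the estimate is biased, and in which direction, cannot be settled from the documents. Differential loss is possible under the withdrawal and unblinding rules, but it is not shown. The range of 1.0 to 3.0 points depends on an assumed gap of 5 to 15 points confined to one arm, at 20% loss; it shrinks in proportion if loss is lower. The exception clause is a lesser, separate fault: it is ambiguous and leaves the primary analysis incompletely specified, with the blinding of analysts as a partial safeguard.

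**What to change.** Replace the population sentence with a named primary method that can do what it claims:

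- **Preferred:** the chained-equations imputation already planned, done separately by arm under coded labels so that analysts stay blind, with baseline and 30-day ASES and the VAS scores in the imputation model. This keeps every randomised participant.
- **Alternative:** a repeated-measures model on day-30 and day-90 ASES, adjusted for baseline. With baseline as a covariate, a participant with no postoperative ASES still contributes nothing. If this model is chosen, either fit baseline as one of the repeated responses or say plainly who is left out.

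State that the method assumes data are missing at random given the variables used. Delete the exception clause. Examine departures from the assumption in prespecified sensitivity analyses instead: the complete-case comparison, and a delta-adjusted imputation in which missing outcomes are set worse than predicted, including in one arm only.

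The cost is wording and slightly more analysis work, with no new participants, visits or measurements. The Trial status section describes the trial as recruiting, so on that footing the change can be made before analysis. The drawback is reliance on missing at random, which is weakest for participants lost before day 30, who contribute only baseline and early VAS data.
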